### Recruitment

A waiver of consent was granted by the McGill University Health Centre Director of Professional Services for this Quality Improvement Intervention. For the purposes of analysis, only the initial closed cohort will be included in the study. New patients who are initiated on maintenance hemodialysis during the study will not be included. Patients who die or are transplanted prior to a MedRec, or who are admitted to hospital and cannot have a MedRec performed, will be accounted for, described, but excluded from the final analysis.

### Assignment of Interventions: Allocation and Blinding

*Sequence generation, Concealment mechanism, Implementation of Allocation*, are all not applicable to this study.

### Who Will Be Blinded?

Clinicians at the control unit will not receive MedSafer reports but will carry out a biannual MedRec as part of usual care. Clinicians rounding on the intervention unit will be made aware of the intervention approximately 2 weeks prior to starting, to allow for familiarization of the MedSafer reports. Four nephrologists will round on the intervention unit during this time, and 3 different nephrologists will round on the control. There is no crossover between physician schedules. Therefore, there is little risk of contamination of the intervention and the control site.

The *Procedure for unblinding* is not applicable to this study.

## Data Collection and Management

### Plans for Assessment and Collection of Outcomes

Baseline demographic data, the best possible medication history data, the most recent glycated hemoglobin as a measure of diabetes control, and creatinine will be collected for both the control and intervention unit from the electronic medical record (EMR), called NephroCare. These data will be input in the MedSafer web-based portal, and deprescribing reports will be generated for patients on the intervention unit.

Following a MedRec, medication changes will be captured from NephroCare and input into the MedSafer software for both the intervention and control units, permitting an analysis comparing deprescribing that took place on the 2 units.

At the time of MedRec, nephrologists will review the medication list of the patient (obtained from the EMR), validate the list with the patient, and then deprescribe when deemed appropriate (based on the MedSafer report). Medication changes will be faxed the same day to patient’s pharmacy. During this process, if a patient advises the clinical team that they are no longer taking a prescribed drug, this medication will be removed from the patient’s medication list in the EMR. If it is discovered that a patient has already discontinued a drug at the time of performing a MedRec, this will not be counted in the primary outcome of deprescribing.

At the end of the intervention, nephrologists who participated in MedRecs will be invited to participate in semi-structured interviews with the study lead to address their perceived facilitators and barriers related to deprescribing on the dialysis unit. Afterward, themes will be developed from the data collection, according to the grounded theory in qualitative research.^
34
^

### Plans to Promote Participant Retention and Complete Follow-up

We do not expect significant loss to follow-up given the intensity that patients on outpatient hemodialysis are monitored and the short timeframe of the intervention.

### Data Management

Manual baseline data entry for all patients will occur in the MedSafer web-based portal with data extracted from the NephroCare EMR by a trained study investigator. Any medication changes that occur are input into NephroCare at the time of performing the MedRec. When a MedRec occurs, the date is noted in the unit “task binder” located on site and accessible to all clinicians. MedRecs are considered up to date if they have been completed in the past 6 months and are only redone in the event a patient is hospitalized.

Before and after the MedRecs have been completed, each patient’s medication and comorbidity data will be updated in MedSafer, and a pre- and post-intervention medication dataset (coded by study ID) will be extracted and stored on a secure server. Analysis will be conducted on these coded datasets to record medication changes and deprescribing.

### Confidentiality

Only [name] will have access to the nominal MedSafer data, which has the identity data encrypted and password protected at the level of the user account. MedSafer patient reports generated by the system must be nominal such that they can be given to the correct patient. These will be printed within the hospital, hand delivered, and stored in a secured area in the dialysis unit until needed. Following completion of the study, the printed MedSafer reports will be securely destroyed.

### Statistical Methods

#### Statistical methods for primary and secondary outcomes

Baseline demographics will be expressed as numbers and percentages for categorical variables and median (interquartile range [IQR]) for continuous variables. Differences between the intervention and control patients will be compared by χ^
2
^ or rank sum as appropriate.

For the primary outcome, we will use a mixed-effects logistic regression model controlling for the unit of intervention. As we expect some baseline differences in patient complexity between the control and intervention units whereby patients on the control unit tend to be more medically complex, we will adjust for the Charlson comorbidity index,^
35
^ median number of medications, and median number PIMs, as fixed effects. Adjusted risk differences will be estimated from the model parameter differences. A similar analysis will be conducted for the key secondary outcome. Analyses will be conducted in Stata Software Version 17 (StataCorp LP, Corpus Christi, USA).^
36
^

There are no planned *interim analyses*.

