## Methods: Participants, Intervention, and Outcomes

### Study Setting

The study takes place on the 2 largest (of 3) outpatient hemodialysis units at the McGill University Health Centre in Montreal, Quebec, Canada. The intervention unit is the Lachine Hospital dialysis unit, and the control unit is the Montreal General Hospital dialysis unit. This assignment was random.

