### Methods for Additional Analyses

A planned subgroup analysis will be conducted by biologic sex and by age category (<65 vs >65). The analytic approach will be the same as that used for the primary outcome analysis.

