^ This is a single-center study, and to influence outcomes such as these likely requires more than 6000 patients (based on our previous study of MedSafer in the acute care setting). This study is also not randomized; we aim to minimize (but cannot eliminate), through statistical adjustment, obvious baseline differences in comorbidities between the control and intervention units. Next, our study is not sufficiently powered to capture differences in rates of represcribing between the control and the intervention group. It should be noted that our study will capture prescribed/deprescribed drugs, and not *dispensed* drugs, or drugs actually taken by the patient. Another caveat is that our dialysis units do not have the support of a pharmacist, and so the MedRec process will be performed by the doctor and nurse on the unit. Finally, our study is taking place at an academic hospital center and so the patients may not resemble those treated in all dialysis centers. That said, the 2 units participating in the study tend to provide dialysis for general nephrology patients, and the intervention unit is attached to our community hospital site.

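### Age and sex are left out of the fixed adjustment set of the primary model, so residual confounding by them is not controlled in a comparison of two non-randomised units

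*Protocol article*

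**What the plan says.** Under the statistical methods for primary and secondary outcomes, the article plans a mixed-effects logistic model for the proportion of patients with at least one PIM deprescribed. It states "we will adjust for the Charlson comorbidity index" and completes the list with "median number of medications, and median number PIMs, as fixed effects". The stated reason is that control patients are expected to be more medically complex. A similar analysis is planned for the key secondary outcome. The same section tests baseline differences between the units but has no rule that carries an observed difference into the model.

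Under Methods for Additional Analyses: "A planned subgroup analysis will be conducted by biologic sex and by age category". Under Plans for Assessment and Collection of Outcomes, the items collected on both units begin with "Baseline demographic data, the best possible medication history data".

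The Discussion says "This study is also not randomized" and directs the adjustment at "obvious baseline differences in comorbidities between the control and intervention units", conceding that these cannot be eliminated. The Study Setting section says of the two units "This assignment was random".

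**The concern.** Each arm is one dialysis unit. Even if the choice of which unit received MedSafer was random, allocating two whole units does not balance patient characteristics between them. Covariate adjustment is the main analytic protection against patient-level confounding, so the covariate list matters more here than in a trial that randomises patients.

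Age has a plausible route to the outcome. Only PIMs flagged by MedSafer count, the ruleset draws on guidelines for older adults, and eligibility starts at 18 years. The number of PIMs records how many drugs are flagged but not which ones, and the Sample Size section itself cites a class-specific deprescribing rate (as low as 5% for sedative hypnotics). The article does not say whether the Charlson index is age-weighted. If it is not, no listed covariate represents age directly. None represents sex.

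At stake is an avoidable bias, of unknown sign, in the primary risk difference. A covariate set extended only after the baseline table has been seen would be open to the charge of post-hoc choice.

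**Working it through.** **The plan's own figure (Sample Size section).** The inputs are 85 and 153 patients, about 90% with a PIM, a 10% control rate, a 15-point increase, two-sided alpha 0.05 and 80% power.

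- Analysable patients: 0.9 × 85 = 76.5 and 0.9 × 153 = 137.7, total 214.2. The stated 214 reproduces; I use 76 and 138.
- Power with pooled variance and no continuity correction: pooled rate 32.8/214 = 0.153; standard error 0.0515 under the null and 0.0559 under the alternative; z = (0.15 − 1.96 × 0.0515)/0.0559 = 0.88; power 0.81. At exact 1:2 allocation the required total is 142 + 71 = 213.

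The sample-size statement holds, and the omission of age and sex does not alter it.

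**Events per parameter** (intercept not counted; current model = unit plus three covariates).

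- Planned rates: 138 × 0.10 + 76 × 0.25 = 32.8 events. 32.8/4 = 8.2; with age and sex, 32.8/6 = 5.5.
- No effect: 214 × 0.10 = 21.4 events. 21.4/4 = 5.4; with age and sex, 21.4/6 = 3.6.

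**Possible bias.** The article gives no age or sex distribution by unit and no association of either with deprescribing, so everything below is assumed: no MedSafer effect, a 10% control rate, and an omitted variable unrelated to the three included covariates.

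*Age, continuous.* Intervention rate = expit[logit(0.10) + years × ln(OR per year)].

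- 5 years older, OR 1.02, 1.03 or 1.05 per year: false OR 1.10, 1.16 or 1.28; shift +0.9, +1.4 or +2.4 points.
- 8 years older, OR 1.05 per year: false OR 1.48; odds 0.111 × 1.48 = 0.164; rate 14.1%; shift +4.1 points.
- 8 years younger, same OR: odds 0.111/1.48 = 0.075; rate 7.0%; shift −3.0 points.

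*One omitted binary covariate* (sex, or age as two groups), 50% prevalence on the control unit. Shift = prevalence difference × (rate with the factor − rate without it), with the two rates set to average 10% on the control unit. The sign reverses if the imbalance reverses.

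| OR of covariate | 5-point imbalance | 10-point | 20-point |
|---|---|---|---|
| 1.5 | 0.2 | 0.4 | 0.7 |
| 2 | 0.3 | 0.6 | 1.2 |
| 3 | 0.5 | 0.9 | 1.8 |

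Over this table, the chance that an unadjusted two-proportion test falsely favours the intervention rises from the nominal 0.025 to between 0.028 and 0.066.

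**The case against.** A reader might infer that any age or sex difference between the units passes straight into the MedSafer effect. The article does not support that. A difference biases the estimate only if the variable still predicts deprescribing after conditioning on Charlson index, number of medications and number of PIMs. Much of the age route runs through the number of PIMs, which is in the model, and the analysis is restricted to patients with at least one PIM. The article suggests no mechanism for sex.

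A reader might also take the subgroup plan as evidence of confounding. It is not: a subgroup analysis asks whether the effect varies by age or sex. What the plan does show is that both variables will be available.

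Nor is adjustment the only safeguard. The article describes choosing two units it regards as similar and leaving out the more complex third, and it admits that adjustment is imperfect. The sizes above are assumption, and the age figures lean high because they treat the whole age effect as separate from the included covariates. The 4.1-point figure pairs the largest assumed imbalance with the largest assumed odds ratio.

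The remedy also has a cost. Under no effect only 3.6 events per parameter remain. An ordinary Firth fit pulls predicted probabilities towards 0.5, which matters when the reported measure is an adjusted risk difference.

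These objections limit the claim and shape the remedy. They do not explain why two available baseline variables stay out of the model in a non-randomised comparison. Nor can the list be read as a detail left to another document, because the article names the covariates and gives its reason for them.

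**Conclusion.** The point holds in a limited form. The stated adjustment set omits age and sex, so residual confounding by them is not controlled in the primary estimate. Whether there is any bias, and in which direction, cannot be derived from the article. Under the assumed values the shift is roughly 0.2 to 4 points upwards and down to about −3 in the reversed extreme case, against a 15-point target. If an age-weighted Charlson index is meant, age is already partly covered. This is a worthwhile, low-cost improvement and not a fatal flaw. It does not touch the larger limit: each arm is a single unit with its own nephrologists, and the article itself says that deprescribing depends on the nephrologist, so unit and intervention effects cannot be separated.

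**What to change.** In the section on statistical methods for primary and secondary outcomes:

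- Add age (continuous, one term) and sex as prespecified fixed effects in the primary and key secondary models, and state which version of the Charlson index is used.
- Report the model without age and sex as a sensitivity analysis.
- Prespecify what happens if sparse data make the logistic fit unstable: a method that keeps the risk difference calibrated, such as a Firth fit with intercept correction, or standardisation, and not ordinary Firth alone.

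This takes a few sentences and no new data. The price is the fall in events per parameter shown above, which is most serious if there is little or no effect. The single-unit-per-arm limit should stay among the stated limitations, since these two covariates do not reduce it.

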### Methods for Additional Analyses

A planned subgroup analysis will be conducted by biologic sex and by age category (<65 vs >65). The analytic approach will be the same as that used for the primary outcome analysis.

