### Eligibility Criteria

#### Inclusion criteria

Outpatients receiving maintenance hemodialysis on one of the two participating units.Aged 18 years and over.One or more PIMs identified.

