### Sample Size

The sample size is fixed to the number of patients in each of the dialysis units (85 patients on the intervention unit and 153 on the control unit). A previous study of MedSafer in hemodialysis estimated ~90% of dialysis patients are prescribed 1 or more PIMs, which is the assumption we will make here as well (N = 214). In our acute care study, we found a baseline rate of PIM deprescribing in the hemodialysis subpopulation of 19.3%. However, in outpatients, deprescribing of sedative hypnotics is often as low as 5%.^
27
^ Therefore, we will estimate a 10% baseline rate of deprescribing. With a 2-sided alpha of 0.05, 80% power, and approximately 1:2 allocation between intervention and control, we can show an increase of at least 15% in the proportion of patients with 1 or more PIMs deprescribed. The statistical code for this calculation is available in the Supplemental Appendix.

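### The age subgroups omit patients aged exactly 65, and the stated subgroup method has no unit-by-subgroup term

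*Protocol article*

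**What the plan says.** The protocol article, Methods for Additional Analyses, gives the subgroup plan in two sentences. The first names the factors and the age cut: "A planned subgroup analysis will be conducted by biologic sex and by age category (<65 vs >65". The second fixes the method: "The analytic approach will be the same as that used for the primary outcome analysis".

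That method is set out under Statistical methods for primary and secondary outcomes: "we will use a mixed-effects logistic regression model controlling for the unit of intervention". On covariates, "we will adjust for the Charlson comorbidity index", together with "median number of medications, and median number PIMs, as fixed effects". Adjusted risk differences are then to be derived from the model. No sex term, age term or product term is listed.

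The inclusion criteria set only a lower age limit: "Aged 18 years and over".

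**The concern.** There are two separate issues.

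First, both inequalities in the age cut are strict, so age 65 has no category. Read literally, those patients leave the age analysis. Otherwise someone must decide where they go after the data are in hand. A pre-specified cut-point is meant to remove that choice.

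Second, a subgroup analysis asks whether the effect differs between groups. The model that the article points to has no term for that difference. If it is refitted within each sex and each age group, every fit uses only part of an already small number of events, and the output is two separate effects with no estimate of the contrast between them. A reader could then take a significant result in one group and a non-significant result in the other as evidence that the effect differs.

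**Working it through.** **Inputs from the article (Sample Size).** Unit sizes: "85 patients on the intervention unit and 153 on the control unit". About 90% are expected to have at least one PIM, "which is the assumption we will make here as well (N = 214". The control rate is 10%, the increase 15 points (so 25% on the intervention unit), two-sided alpha 0.05 and power 80%.

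**Assumed, because the article does not give it.** The share of patients in a subgroup: 30% to 60%, with 50% as the reference case.

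**The article's own figure.** 0.9 × 85 = 76.5 and 0.9 × 153 = 137.7, total 214.2, which matches N = 214. Power for two proportions with pooled variance and no continuity correction, at 76 versus 138:

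- pooled rate = (0.25 × 76 + 0.10 × 138)/214 = 0.153
- null SE = sqrt(0.153 × 0.847 × (1/76 + 1/138)) = 0.0515
- alternative SE = sqrt(0.25 × 0.75/76 + 0.10 × 0.90/138) = 0.0559
- power = Φ((0.15 − 1.96 × 0.0515)/0.0559) = 81%

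The smallest increase with 80% power is 14.75 points. The article's calculation is reproduced.

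**Age boundary.** Eligible ages run from 18 upwards without a gap; the age categories have a gap at 65. The number of patients aged exactly 65 is not given, so the effect of the gap cannot be sized.

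**Events per slope, full cohort.** Expected events = 0.25 × 76.5 + 0.10 × 137.7 = 19.1 + 13.8 = 32.9. The primary model has four slopes: unit (which is also the intervention contrast), Charlson index, number of medications and number of PIMs. 32.9/4 = 8.2 per slope.

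**Events per slope if the same model is refitted within a subgroup.** The power column uses the formula above, with unrounded sizes.

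| Share of patients | Expected events | Events per slope (÷ 4) | Power for +15 points |
|---|---|---|---|
| 60% | 19.7 | 4.9 | 61% |
| 50% | 16.4 | 4.1 | 54% |
| 40% | 13.2 | 3.3 | 46% |
| 30% | 9.9 | 2.5 | 37% |

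The larger partner of a 30% subgroup would have 0.7 × 32.9 = 23.0 events, or 5.8 per slope, still below the full-cohort 8.2.

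**Comparing two separate results.** With the same true +15 points in two equal, independent subgroups, the chance that exactly one is significant is 2 × 0.538 × (1 − 0.538) = 0.497, about half. At a 40:60 split it is 0.458 × 0.391 + 0.609 × 0.542 = 0.51.

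**One full-cohort model per factor.** Six slopes (the four above, the subgroup and unit-by-subgroup): 32.9/6 = 5.5 events per slope. With sex and age and both product terms in one model there are eight slopes: 32.9/8 = 4.1, the same as a half-size separate fit.

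**Precision of the contrast, equal halves (38 versus 69).** Subgroup SE = sqrt(0.25 × 0.75/38 + 0.10 × 0.90/69) = 0.079. SE of the difference between two subgroups = 0.079 × sqrt(2) = 0.112. Half-width = 1.96 × 0.112 = 0.219, about 22 points. The approximate power of an interaction test on this scale is 33% for true effects of 15 versus 0 points, 45% for 25 versus 5, and 81% for 30 versus 0.

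**The case against.** The article never says that the model is refitted separately, and the same mixed logistic model with a product term added could be called the same approach. The text is a condensed journal account. A statistical analysis plan that is not shown may specify an interaction, and leaving such detail to it is ordinary. The article also announces no subgroup p-values, decision rule or claim, and places these analyses under additional methods. The age cut looks like a slip of one symbol.

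Much of this stands. A reader might infer that the plan prescribes separate fits and will never test whether the effect differs; the article supports neither statement. It supports only that the approach it names lists no term for the difference, and that refitting is the natural way to apply that approach to a subgroup.

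A reader might also infer that the imprecision of about 22 points is a cost of the stated method. It is not. It follows from the fixed sample size and is essentially the same with an interaction model. Nor does every interaction model relieve the sparseness: one carrying both factors has 4.1 events per slope, no better than a half-size separate fit.

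The age gap is not answered by any of this, because the cut-point is stated in the article itself.

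**Conclusion.** The age categories are wrong as written. This holds without assumptions, although its effect cannot be sized and is probably small.

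The criticism of the method holds conditionally. The approach as stated contains no unit-by-subgroup term. If it is applied by refitting within subgroups, it is sparse and does not estimate the difference in effect, and setting one significance result against the other would mislead about half the time when the true effects are equal.

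These figures rest on the article's 10% and 25% rates and its 90% PIM share, on an assumed split, and on unadjusted calculations that ignore clustering, as the article's own calculation appears to. Events per slope is a rule of thumb. Fewer events would make matters worse: with 10% in both units, a half-size subgroup has 0.10 × 107.1 = 10.7 events, or 2.7 per slope.

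The primary result is unaffected. Severity is minor.

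**What to change.** Write the age categories as <65 versus >=65.

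State that each subgroup factor is examined in one model on the full cohort: the primary model plus the subgroup and a unit-by-subgroup term. Do this for sex and then for age, not for both together. Report the adjusted risk difference in each subgroup and the interaction estimate with its 95% CI, name its scale, and label the results exploratory.

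The cost is two sentences and no new data. If the analysis plan already specifies such a model, only the age symbol and a cross-reference are needed. The change supplies the right estimate but not precision: an interval of about plus or minus 22 points is wider than the 15-point effect the study is sized for, so a null interaction result should not be read as showing equal effects.
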